## Methods

### Study Design and Setting

The quantitative component of this study is a retrospective longitudinal observational analysis of data collected during routine care within KPWA, a large nonprofit integrated health care and insurance coverage system in the Pacific Northwest serving over 700,000 individuals across Washington State [30]. The qualitative component consists of a prospective observational study of patient visits and an interview-based study involving KPWA patients and health care staff from KPWA and partnering organizations.

KPWA operates in more than 46 clinical locations, including primary care clinics, specialty centers, urgent care facilities, and EDs. It also maintains a contracted network for services such as specialty addiction treatment and hospital care. Primary care in KPWA is delivered through team-based models involving medical assistants, nurses, and primary care providers [31]. KPWA provides a full spectrum of services for identifying and treating SUD [32-34]. All adult group practice patients are screened annually for substance use and further assessed using standardized tools if they screen positive. Treatment options include brief counseling, pharmacotherapy, and referrals to detoxification services, which may be delivered in either inpatient or outpatient settings. A mental health access center serves as a centralized hub for coordinating referrals and authorizations for specialty addiction care [33]. Most specialty SUD treatment is provided by external treatment programs via a large, contracted care network.

### Ethical Considerations

The Kaiser Permanente (KP) Institutional Review Board granted ethical approvals for the aims 1 and 2 activities. Waivers of consent and HIPAA (Health Insurance Portability and Accountability Act) Privacy Rule Authorization were granted to access, collect, and use data from secondary data sources for this research under 45 Code of Federal Regulations (CFR) 46.116(d) and 45 CFR 164.512(i). This study was deemed to have no more than minimal risks, and it would not be otherwise feasible to conduct this study without these waivers. The qualitative data collection will require informed consent and waivers of consent and will be submitted for KP Institutional Review Board review and approval before execution of aim 3. We will recruit patients via multiple modes (phone, email, or mailed letter with a US $2 preincentive) [35] to invite them to participate in the interviews. Clinician and patient participants will receive US $75 for their time.

### Quantitative Study Population

This study’s cohort will include patients who receive care for SUD. Eligible patients are adults aged 18 years and older with an incident SUD identified between January 1, 2017, and May 31, 2025. We will include both group practice enrollees, who receive most of their care from internal KPWA-owned and operated clinics, and KPWA health insurance plan enrollees who primarily receive care outside the internal delivery system (IDS). Incident SUD is defined as meeting any of the following criteria at a clinical encounter with no prior SUD indicators in the past 6 months: (1) a newly documented SUD diagnosis, or (2) two or more *DSM-5* (*Diagnostic and Statistical Manual of Mental Disorders, Fifth Edition*) symptoms reported on standardized patient symptom checklists. The index date will be the date of the qualifying incident SUD event. The 6-month “washout period” is used to define new treatment, modeled on National Committee on Quality Assurance definitions [36], but we may explore the sensitivity of sample definitions using other time frames, such as 60 days [37]. For patients who have been enrolled in KPWA for less than the length of the washout period, we will consider their first SUD event to be an incident SUD event. Provisionally, multiple qualifying incident SUD events from the same patient will be included in the analysis (see details in Statistical Analyses). Patients will be excluded from the analyses if they have opted out of research participation with the health plan (≈0.2%).

The analytic sample will be split into distinct study subcohorts comprising patients with incident SUD identified in the specific clinical settings. We anticipate using five subcohorts, including: (1) primary care, (2) urgent care, (3) ED or hospital, (4) behavioral health, and (5) all other settings. These locations are identified based on EHR and insurance claims data that code clinic departments, places of service, encounter types, and SUD diagnosis data available in each location (Table 1). Once patients are identified as having an incident SUD and meeting the inclusion criteria described above, they enter the initial state of the MSM.

**Table 1. T1:** Study subcohorts defined by the clinical setting in which an incident substance use disorder event occurs. Incident SUD^a^ events are identified for adult patients aged 18 years and older and are categorized into 1 of the 5 subcohorts in this table.

Cohort	Location description	Specification of the triggering event
1	Primary care	Documentation of an SUD diagnosis OR 2+ SUD symptoms as part of follow-up assessment after a positive population-based SUD screen in specified setting
2	Urgent care	Documentation of an SUD diagnosis OR 2+ SUD symptoms as part of follow-up assessment after a positive population-based SUD screen in a specified setting
3	Behavioral health	Documentation of an SUD diagnosis OR 2+ SUD symptoms as part of follow-up assessment after a positive population-based SUD screen in a specified setting
4	All other settings	Documentation of an SUD diagnosis OR 2+ SUD symptoms as part of follow-up assessment after a positive population-based SUD screen in a specified setting
5	Emergency department or hospital	Documentation of an SUD diagnosis in the specified setting

a SUD: substance use disorder.

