### States for the MSMs

States will capture 3 types of events related to SUD care: initial states, transient states, and terminal states. Defining states requires a balance of specificity to produce actionable information, and parsimony to allow for an estimable statistical model with accurate estimates and smaller SEs.

Initial states in the MSMs represent the clinical settings that triggered an incident event at the start of an SUD care episode, corresponding to the 5 subcohorts in Table 1.

There are 3 types of transient states. The first type is care states, which include different types of care provided in the health care system to treat the SUD, defined by combinations of setting and service type (Table 2). We opted to define 15 preliminary SUD care states based on a combination of 3 settings and 5 service types. The second type of transient state is temporary discontinuation of care. Entry into the temporary discontinuation care state is triggered using a clinically meaningful threshold for time elapsed between SUD treatment visits. The last transient state is SUD remission, which represents an improvement in the patients’ disease.

**Table 2. T2:** Transient states and terminal states are represented in the multistate models.

Category	States included	Description
Transient states	A total of 17 transient states include 15 care states derived from crossing 5 service types with 3 care settings; temporary discontinuation of SUD^a^ care; and remission of use disorder.	Care states Service types Evaluation and assessment Behavioral treatment and counseling Prevention, education, and case management Pharmacotherapy Other service Settings Outpatient Intensive outpatient Inpatient or residential Other transient states Discontinuation of SUD care A lack of SUD care over a specified period^b^ Remission of use disorder Low risk score on alcohol and substance use screen; clinically meaningful reduction on screening scores or <2 symptoms on *DSM-5*^c^ checklist; SUD remission diagnosis
Terminal states	4 states representing the end of a care episode	Death, derived from dates in health care enrollment records or Washington State death data Loss to follow-up, defined as at least 31 days without KPWA insurance coverages Ceased SUD care (no medication fills or services with a qualifying SUD diagnosis for more than 194 days Administrative censoring (in the middle of a care episode when data collection ends)

a SUD: substance use disorder.

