b Temporary discontinuation will be defined separately for each care state using an appropriate threshold for time elapsed between visits that reflects acceptable gaps in care for that specific state. All of these periods will be shorter than 194 days to distinguish temporary discontinuation from ceasing substance use disorder care.

c *DSM-5*: *Diagnostic and Statistical Manual of Mental Disorders, Fifth Edition*.

Terminal states indicate the end of an SUD care episode (Table 2), such as ceasing SUD care.

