### Statistical Analyses

#### Aim 1: Apply MSMs to Comprehensively Characterize SUD Care Transitions

Separate MSMs will be run for each of the 5 subcohorts specified in Table 1. The 5 subcohorts are mutually exclusive. All prespecified states that are anticipated will be considered. States may be collapsed to address states with a small number of events, and new states may emerge if they occur with sufficient frequency (eg, concurrent receipt of pharmacotherapy and behavioral treatment and counseling). When collapsing or expanding states, we will strike a balance between clinical interpretability and reliable parameter estimation. As a general guideline, ≥40‐50 transition events from *S*_*j*_ to *S_j_* per covariate helps ensure stable hazard ratio estimates and corresponding SEs, but if collapsing states compromises the clinical interpretability of the results, we will adopt a more permissive threshold of at least 10 transition events per covariate for modeling [58]. This criterion will first be applied to define states; specifically, a minimum of 40 (or 10 under the more permissive threshold) transition events is required to define a state, allowing inclusion of 1 covariate in the transition model. When transitions are sufficient to include covariates in the model, at least 40 × *m* transition events are required. Covariate selection for each transition model, given the number of transitions, is described below. Follow-up time or care episode duration is defined as the interval from entry into the initial state (time 0) to entry into a terminal state.

Figure 1 provides a graphical representation of a simplified MSM illustrating potential care pathways. In this example, patients who meet the inclusion criteria and are identified as having an incident SUD in primary care enter the initial state *C*_1_. Patients then transit into 1 of 15 care states (*S*_1_, ... ,*S*_15_) defined by a service type and setting. From these states, patients may transition to temporary discontinuation of care, *D*, or an SUD remission state, *R*. Transitions between the transient states (care states, temporary discontinuation, and SUD remission) are bidirectional, whereas any transition to a terminal state (*T*_1_, ..., *T*_4_) is unidirectional, reflecting that patients cannot leave terminal states once they are entered in MSMs. At the end of follow-up, patients occupy 1 of the 4 terminal states.

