For simplicity, we omit transition-specific subscripts for the parameters $\left(\eta ,k_{0},\beta \right)$. In the model, $s(\log(t)|\eta ,k_{0})=\sum_{i=1}^{k_{0}}\eta_{i}B_{i}(\log(t))$ represents the log cumulative baseline intensity function, which we model flexibly using restricted cubic spline basis functions (also known as natural cubic splines) $B_{i}(\cdot )$, with corresponding coefficients $\eta_{i}$. The number of knots, $k_{0}$, determines the number of basis functions and thus the flexibility of the baseline intensity functions. For covariates *z*_*i*_(*t*), the coefficients β represent the log hazard ratios at time t. The unknown parameters to be estimated or selected from data are $\left(\eta ,k_{0},\beta \right)$. We will use the Akaike information criterion based on data to select the number of knots, with lower Akaike information criterion values indicating better model fit. The regression coefficient parameters (η,β) will be estimated by using the maximum likelihood approach for statistical inference [62,63]. For each transition, we will include prespecified covariates for adjustment when the number of transitions allows (at least 10 transition events per covariate), and if additional covariate selection is required, variables that are statistically significant at the 5% level based on Wald tests will be included [64]. The estimated transition intensities are transformed to a transition probability from states j to k at time t since entry into state j at time s (s<t, s and *t*>0), by integrating, $p_{jk}(s,t)=\exp\left\{-\int_{s}^{t}q_{jk}(u,z(u))\;du\right\}$.

Multiple incident SUD events may be observed within the same patient (see Quantitative Study Population). For example, a patient may have an incident SUD event, eventually experience a terminal state such as ceasing SUD care (eg, one who receives no SUD care for 194 days), and then experience a second incident SUD event. Including multiple incident events from the same patient within the same subcohort in the MSM framework may introduce within-patient correlation and reflect care pathways that differ from those of the initial episode. We will account for within-patient correlation using a sandwich variance estimator for the parameter estimates. The number of prior incident events will be included as a covariate or used as a stratification factor, depending on its distribution.

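### The incident-event washout (6 months) is shorter than the gap that closes an episode (more than 194 days), and no rule requires the earlier episode to have ended, so a qualifying visit can fall in two episodes

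*Protocol article*

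**What the plan says.** All references are to the protocol article.

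- **Start of an episode** (Quantitative Study Population). A patient has an incident SUD event on "meeting any of the following criteria at a clinical encounter with no prior SUD indicators in the past 6 months". The criteria are a newly documented SUD diagnosis, or two or more DSM-5 symptoms on a checklist. For the length of the washout, "we may explore the sensitivity of sample definitions using other time frames, such as 60 days".
- **Repeat events** (same section). Provisionally, "multiple qualifying incident SUD events from the same patient will be included in the analysis".
- **End of an episode** (States for the MSMs, Table 2). The terminal state for ceased care requires "no medication fills or services with a qualifying SUD diagnosis for more than 194 days".
- **Shorter gaps** (Table 2, footnote b). These count as temporary discontinuation, with thresholds set per care state: "All of these periods will be shorter than 194 days to distinguish temporary discontinuation from ceasing substance use disorder care".
- **Return to care** (Statistical Analyses, Aim 1). "Transitions between the transient states (care states, temporary discontinuation, and SUD remission) are bidirectional". A patient who comes back from temporary discontinuation is thus still in the same episode.
- **Order of repeat episodes** (Aim 1, paragraph on multiple incident events). An example has a patient reach a terminal state "and then experience a second incident SUD event". Within-patient correlation is handled by a sandwich variance, and the number of prior incident events enters as a covariate or stratum.
- **State occupancy** (Aim 1, text after Figure 1). At any time after entry, a patient is in exactly one of the 21 states.

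**The concern.** One rule opens episodes and another closes them, and the opening rule can be met first. Between the two thresholds the earlier episode is still running, in temporary discontinuation, while a qualifying encounter already counts as a new index event. Applied literally, the encounter is entered twice: as a transition from discontinuation to a care state in episode 1, and as time 0 of episode 2.

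From that visit on, the patient is followed on two clocks. Later transitions and the eventual terminal event can enter twice. If the visit is in a different setting from the first index event, the same person-time feeds two of the separately fitted subcohort models. The count of prior incident events also rises for what is a return to care. The sandwich variance deals with correlation between a patient's episodes. It does not remove duplicated follow-up from the point estimates.

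The 60-day alternative widens the gap between the two rules. If only the washout is shortened, a difference from the main result could come from the new sample definition or from the duplicated episodes, and the two could not be told apart.

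**Working it through.** The article gives no figure for this point, so there is nothing to reproduce. The check is a day count, followed by an illustration under a stated assumption.

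**Inputs from the article**
- Washout: 6 months in the main definition, 60 days as a possible alternative (Quantitative Study Population).
- Ceased care: gap of more than 194 days (Table 2).

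**Step 1. Six months in days.** Counting six calendar months forward from every date between 1 January 2017 and 31 May 2025 gives 181 to 184 days. For comparison, 194 / 30.4375 = 6.37 months.

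**Step 2. Overlap window.** Let g be the days since the last SUD contact. A qualifying encounter is a new incident event if g > washout. The earlier episode is still open if g ≤ 194. Both hold for washout < g ≤ 194, which is 194 − washout days.

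| Washout | Days in both rules | Length |
|---|---|---|
| 184 days | 185 to 194 | 194 − 184 = 10 |
| 181 days | 182 to 194 | 194 − 181 = 13 |
| 60 days | 61 to 194 | 194 − 60 = 134 |

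Reading the inequalities as strict or not, and allowing 180 days for six months, moves the main window to between 9 and 15 days and the 60-day window to between 133 and 135 days.

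**Step 3. Illustrative share of returns.** The article gives no distribution of gaps between visits. Assume exponential gaps with mean m of 60, 90 or 120 days. Among returns within 194 days, the share in the window is

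(exp(−w/m) − exp(−194/m)) / (1 − exp(−194/m)), where w is the washout.

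For m = 60 and w = 184: (0.04658 − 0.03943) / (1 − 0.03943) = 0.7%.

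| Mean gap m | w = 184 | w = 181 | w = 60 |
|---|---|---|---|
| 60 days | 0.7% | 1.0% | 34% |
| 90 days | 1.5% | 2.0% | 45% |
| 120 days | 2.2% | 2.8% | 51% |

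These are upper bounds under the assumption, because they count every return. Only an encounter with a newly documented diagnosis or at least two symptoms can be an index event.

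**Step 4. Effect of a closing rule.** If a new event may start only after a terminal state, no visit can be in two episodes, whatever the washout. Setting both thresholds to more than 194 days would also give a window of 0 days, but is not needed.

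**The case against.** The strongest reply is that sequential episodes are plainly intended. The worked example puts the terminal state before the second event, an episode is defined as running to a terminal state, the subcohorts are described as mutually exclusive, and a patient is in one state at a time. On this view only a tie-break is missing, of the kind a condensed article leaves to the full protocol. The intent is probably as described. But the example is only an example, and no rule makes it binding. The article states two numeric thresholds that collide when applied as written, which is more than an omitted detail.

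A second reply is that six months may be loose wording for 194 days, since the washout is said to follow a quality-measure definition. If so, the main overlap shrinks to 0 or 1 day. The article does not say this, and the 60-day overlap would remain.

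Three further points stand and limit the finding:

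- The two clocks need not match. The washout looks at SUD indicators, and ceased care looks at fills and services with a qualifying diagnosis. If indicators are the broader set, fewer visits fall in the overlap.
- A reader might infer that under the 60-day definition every return at 61 to 194 days is counted twice. The text does not support that. A care state can rest on a procedure or medication solely indicated for SUD without an accompanying diagnosis, and such a return need not be an index event.
- A reader might also conclude that the 60-day analysis could not be interpreted at all. It is optional, and the article does not say that the 194-day rule would stay fixed alongside it. The difficulty arises only if it does.

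**Conclusion.** The point holds as a conflict between two stated rules. A qualifying encounter from day 182 or 185 (depending on the half-year) to day 194 after the last SUD contact meets the definition of a new incident event while the earlier episode is still open, against the one-state-at-a-time structure and the sequence in the article's own example.

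For the main analysis the consequence is probably small: a window of 10 to 13 days, and at most about 0.7% to 2.8% of returns within 194 days. For the 60-day analysis it could be large, with a 134-day window and an upper bound of about 34% to 51%, but only if that analysis is run and the 194-day rule is left as it is.

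The day counts rest on reading six months as calendar months and on a common starting point for both clocks. The percentages rest on the assumed exponential gaps and carry no more weight than that. Episodes already ended by loss of coverage do not overlap. No effect on any particular estimate has been shown. The case for acting is that this rule builds every episode and clock, and that correcting it costs almost nothing.

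**What to change.** 1. State that a new incident SUD event counts only after the patient's previous episode has reached a terminal state, and that a qualifying visit before then is a return to care in the open episode.
2. For the 60-day sensitivity analysis, choose one rule in advance: apply the shorter washout to a patient's first episode only, or change the ceased-care threshold together with the washout. If that threshold is shortened, the temporary-discontinuation periods must be kept below it, as footnote b now requires relative to 194 days.
3. Use one form of the ceased-care threshold. Table 2 requires a gap of more than 194 days, while the example in Aim 1 speaks of 194 days.

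The 6-month washout need not change. The cost is a sentence or two, one programming rule and a very small loss of index events. Final quantitative data collection is expected in November 2027, so the rule can be set before the final data are assembled.

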### Quantitative Data Sources

Data for this study will be drawn from KPWA’s EHR, health insurance claims, membership enrollment records, and death data, as well as additional cause of death data collected from Washington State. KPWA EHR data provide comprehensive encounter-level records on all health services received by members. These data include information on all in-person and virtual encounters, including telephone visits and secure messages. This information is primarily captured through real-time utilization and clinical information abstracted from the EpicCare EHR. Data entered into the EHR are maintained in a relational database that allows linkages across individuals, encounters, and health measures. Membership enrollment records document individuals’ enrollment history, source of insurance, benefit design, demographic information, and medical bill financial assistance requests. Health care claims submitted by contract providers and facilities will be used to capture services not provided within KPWA’s IDS. For instance, all ED care is provided outside of the IDS. KPWA obtains nearly 99% complete data of externally provided services within 6 months of delivery. From Washington State, we will obtain death data containing causes and dates of death, provided that these events occur in the state of Washington [38]. The publicly available social determinants of health (SDOH) Database created by the Agency for Healthcare Research and Quality (AHRQ) will be used to ascertain socioeconomic characteristics (eg, per capita income and unemployment rate) and health care resources (eg, number of physicians and number of hospital beds) in patients’ residence county.

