How often and where is guideline-concordant care achieved? We will analyze several health care quality measures, including those published by the National Committee on Quality Assurance [36,70,71] and others [72,73]. These monitor initiation of care, or the receipt of prespecified health services following an incident SUD event; engagement in care, defined as having a minimum number of qualifying services after initiating care; and adequacy of treatment, which captures whether quantity or duration of treatment over time is sufficient. Achievement of these measures can be ascertained from the states in the MSM model. Multimedia Appendix 1 contains details about how we will operationalize these quality measures using estimates from the fitted MSMs. For example, a National Committee on Quality Assurance quality measure monitors follow-up for patients who have an acute care encounter for SUD. This measure monitors the percentage of patients who obtain follow-up SUD care after an ED visit over 7-day and 30-day timeframes. Thus, among patients in the ED and hospitalizations subcohort whose incident SUD event is in an ED setting, we will estimate transition probabilities capturing the likelihood of transitioning from the initial state to any SUD care state within 7-day or 30-day. We will estimate measures reflecting care engagement and adequacy of treatment by estimating the expected length of time in a pharmacotherapy state or the expected number of visits to qualifying states over the duration of time specified in Multimedia Appendix 1.

How does the probability of occupying terminal states differ across patient subgroups? Within study subcohorts, we will conduct descriptive analysis comparing occurrences of terminal states across patient subgroups. For instance, we will compare terminal states at selected time points (eg, 1-year after cohort entry) across mutually exclusive subgroups defined by patient SUD type (eg, sole opioid, alcohol, or cannabis use disorder vs multiple SUDs). Comparisons of terminal states will help provide insights into whether outcomes differ for specific groups of patients who have incident SUD events in each setting [28].

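### Incident status is unverified for members enrolled under 6 months, and no planned analysis separates them from members with a full look-back

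*Protocol article*

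**What the plan says.** All of the entry rules are in the protocol article, Quantitative Study Population. An event is incident if it occurs "at a clinical encounter with no prior SUD indicators in the past 6 months". The washout "is used to define new treatment, modeled on National Committee on Quality Assurance definitions". The exception follows: "For patients who have been enrolled in KPWA for less than the length of the washout period, we will consider their first SUD event" as incident. No minimum or continuous enrollment is required, and the only exclusion stated is this: "Patients will be excluded from the analyses if they have opted out of research participation with the health plan" (about 0.2%). On robustness, the text offers "we may explore the sensitivity of sample definitions using other time frames, such as 60 days".

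Under Quantitative Data Sources, the service history is that of members: "KPWA EHR data provide comprehensive encounter-level records on all health services received by members". Claims add services from contracted providers. Membership records hold enrollment history. No source is named for care received before enrollment.

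Under Aim 2, the quality measures include "initiation of care, or the receipt of prespecified health services following an incident SUD event", followed by engagement and adequacy of treatment.

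**The concern.** The washout is there to support the statement that treatment is new. For a member enrolled three weeks before the index date, the absence of earlier SUD records shows three weeks without recorded care, and says nothing about the months before. Someone who joins the plan while established on medication or in counseling will at some point have a first KPWA encounter carrying an SUD diagnosis. That encounter meets the Table 1 trigger and becomes time 0, although clinically it may be the next visit of an existing course.

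For such a patient, time to pharmacotherapy or counseling measures the interval to the next scheduled contact and does not measure access after identification. The study wants to tell the health system how quickly newly identified patients reach care and how often they initiate and engage. Mixing in continuing patients changes what those estimates describe, and readers would have no output from which to judge by how much.

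**Working it through.** The protocol gives no figure that depends on this rule, so there is none to reproduce. The check has two parts.

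**1. Does anything in the plan separate or detect these patients?**

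- *Look-back.* It equals the smaller of 6 months and time enrolled. For the excepted members it is therefore 0 to just under 6 months.
- *Optional 60-day washout.* This shortens the window for everyone. Fewer members then fall under the exception, but those with an event soon after joining remain in it, and they have the least history. No contrast between full and truncated look-back results.
- *Number of prior incident events* (Statistical Analyses, Aim 1). This counts events in the study data. Treatment before enrollment contributes zero.
- *Covariates section.* It lists insurance history by type of coverage, but not length of enrollment or of look-back.
- *Sensitivity analyses under Aim 1.* These stratify by number of outpatient visits, calendar period and SUD type.
- *Limitations.* These mention care outside the system and misclassification in general, but not unverified incident status at entry.

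So nothing planned identifies the group. The outcomes depend on the same event: time 0 is entry into the initial state (Aim 1), and Table 4 derives hitting probability, first passage time and expected visits from there.

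**2. How large could the effect be?** All four inputs are assumptions; the documents give none of them.

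- f, share of index events with under 6 months of enrollment: 5% to 20%
- q, share of those already in treatment: 10% to 60%
- p_new, initiation among truly new cases: 30%
- p_prev, initiation among continuing patients: 60% or 90%

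Observed initiation = (1 − f·q)·p_new + f·q·p_prev, so bias = f·q·(p_prev − p_new).

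| f | q | f·q | p_prev | Observed | Bias (points) |
|---|---|---|---|---|---|
| 5% | 10% | 0.5% | 60% | 30.15% | 0.15 |
| 10% | 30% | 3% | 60% | 30.9% | 0.9 |
| 10% | 30% | 3% | 90% | 31.8% | 1.8 |
| 20% | 60% | 12% | 60% | 33.6% | 3.6 |
| 20% | 60% | 12% | 90% | 37.2% | 7.2 |

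Across the grid, continuing patients are 0.5% to 12% of index events and the bias is 0.15 to 7.2 points.

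**The case against.** The strongest defense is that the study is exploratory, describes pathways within one system and states the rule openly. New members are part of the population served. Removing them from the main cohort would condition on 6 months of enrollment and reduce transition counts in five separate models that already work to thresholds of 40, or 10, events per covariate. That stands as an argument against exclusion. It does not argue against a flag and a parallel report.

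The direction of bias is also not certain. Most specialty SUD care is external, with referrals and authorizations coordinated centrally (Study Design and Setting), so a new member may face a break in care. Privately paid care may go unrecorded (Limitations). Some continuing patients could therefore look slow or uninitiated. This stands, and it is why the direction is given only as probable.

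A reader might go further in four ways that the documents do not support:

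- *That short-enrolled members skip the washout altogether.* They do not: a member enrolled for five months is checked over five months, and some of the group are truly new.
- *That anyone returning after a coverage gap re-enters as incident.* Table 2 does close an episode on "Loss to follow-up, defined as at least 31 days without KPWA insurance coverages", but the text does not say that the enrollment clock restarts. The exception concerns a patient's first SUD event, which argues against that reading. This is a point to clarify.
- *That follow-up after an emergency department visit is distorted in the same way.* That measure starts from the visit itself, and a new member seen there for SUD belongs in the denominator whatever came before.
- *That the bias is worst in particular settings or insurance types.* No figure in the document supports a ranking.

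**Conclusion.** The concern holds in a limited form. The entry rule cannot verify new treatment for members enrolled under 6 months, and no planned analysis shows what difference they make. Initiation, first passage time and engagement may be biased as a result, probably upward for uptake and downward for waiting time, on the assumption that continuing patients reach recorded care sooner than new ones.

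The size is unknown. The range of near 0 to about 7 points on initiation rests wholly on the assumed inputs. A reader might arrive at 5 to 10 points by supposing that 10% to 20% of all index events are continuing care with 80% initiation (0.90 × 0.30 + 0.10 × 0.80 = 0.35; 0.80 × 0.30 + 0.20 × 0.80 = 0.40). The documents do not support that. With 20% of index events in short-enrolled members, the upper figure would require every one of them to be already in treatment.

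**What to change.** Using the enrollment history already held, flag each index event preceded by less than 6 months of enrollment. Prespecify that initiation, wait-time and engagement estimates are also reported restricted to, or stratified by, members with a full 6-month look-back, with the remainder labelled 'incident status unverified'. The main cohort can stay as defined. State in the population definition that, for members returning after a coverage gap, KPWA records from before the gap count toward the washout. Add the issue to the Limitations.

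The cost is one derived variable, one extra set of outputs, and wider intervals in the restricted estimates, where sparse transitions may need more collapsing of states. In return, the flag shows what share of index events is affected, which at present cannot be judged.
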